## Abstract

**Objectives:**

Given the increasing trend of care transition from healthcare settings to patients’ own home, patients and their family caregivers should take more responsibilities for care at own home. This study is going to investigate the effect of a transitional care program from hospital to own home using a digital messaging application on patients’ undergoing coronary artery bypass graft (CABG) surgery and their family caregivers’ health outcomes.

**Methods:**

A parallel randomized controlled trial study will be conducted in a hospital in a metropolis located in southwestern Iran. Sampling will be performed sequentially and the eligible dyad of patients and family caregivers will be randomly assigned to intervention and control groups. The intervention group will receive a transitional care program for 8 weeks using the WhatsApp on the mobile phone based on the person-centered care approach, but the control group will receive routine care for patient’s transition. Data collection will be conducted at baseline, immediately after the intervention, and two months after the intervention using demographic questionnaire, Cardiac Self-Efficacy Scale (CSES), MacNew Heart Disease Health-Related Quality of Life questionnaire (MNHD-Q), Cardiac Symptom Scale (CSS), Morisky Medication Adherence Scale, and Caregiver Burden Scale (CBS). Descriptive and inferential statistics will be used for data analysis.

**Conclusions:**

The results of this study will allow evaluating the effectiveness of an innovative transitional care program to patients’ own home using a digital messaging application. If the transitional program is shown feasible and effective it can be incorporated into existing care programs and stimulate further studies on the use of digital solutions for improving the continuity of care in own home.

## Introduction

1.

Cardiovascular disease (CVD) is one of the most common non-communicable diseases worldwide and about 17.9 million people die each year from it, and more than three-quarters of them are in low and middle-income countries (1). In Iran, CVD is rapidly increasing, so that in 2016, 43% of all deaths were due to CVD (2).

Many patients with CVD who do not respond to medications undergo a coronary artery bypass graft (CABG) surgery (3). Although heart surgery saves patients from death, it is accompanied with adverse and durable consequences on the patient’s life. Signs and symptoms experienced by patients after a CABG surgery include angina, dyspnea, fatigue, depression, sleep problems, pain at the surgical site, swelling of the legs, cardiac dysrhythmia, anxiety, and anorexia. These consequences continue even after discharge from the hospital (4–7).

Patients undergoing a CABG surgery are not only seeking to increase their life expectancy but also to improve their quality of life (QoL). The poor QoL of these patients after surgery is associated with the severity of disease, lower survival, referral and readmission to the hospital, and reduced functional activities (8). Therefore, strategies such as providing care training and managing the patient’s physical and mental problems should be used to help them return to normal daily life and maintain optimal QoL (9, 10).

Active patient participation is one of the important principles in the chronic disease care program aiming at increasing self-management and control of risk factors (11). However, these programs are often designed by healthcare professionals, and patient participation in the preparation of care plans often is ignored (12). In this regard, the World Health Organization (WHO) has recommended person-centered care (PCC) as a key element in the high-quality care among patients with chronic conditions (13). The PCC approach focuses more on the patient, his/her needs, preferences, and values than the disease (14).

One of the basic and central concepts for patients with CVD and in the PCC approach is self-efficacy (15, 16), which influences patients’ QoL and health (17). Self-efficacy is the judgment of what one thinks on one can do (18). Theoretically, self-efficacy can be modified and interventions can change it (17).

Patients undergoing CABG surgery usually need support from their spouses or family members for postoperative care and cardiac rehabilitation. Family caregivers often experience concerns about surgical problems and uncertainty about the patient’s future health status (19, 20). A recent study found that family caregivers often face challenges after the CABG surgery including the provision of social support, managing behavioral problems, taking on extra chores at home, and monitoring patients’ symptoms (21). Therefore, caregiving’s burden experienced by family caregivers of patients undergoing the CABG surgery and the provision of appropriate interventions to reduce these problems should be addressed (22).

Proper follow-up of patients undergoing the CABG surgery in the post-discharge period based on the transitional care program from hospital to own home can reduce the readmission rate and the incidence of adverse events (6). The provision of a comprehensive and well-codified follow-up and transitional care program for patients to recover after heart surgery is crucial (23). It can discover potential and actual patient problems and provide an opportunity to use a correct method for patient care management (24, 25).

Transitional care program consisting of patient education helps maintain independence in self-care and improve QoL (26). In recent years, a special attention has been made on transitional care for the safe transfer of patients between different healthcare levels and environments to maintain continuity of care. Transitional care includes transfers between the home, hospital, other care settings such as nursing homes, and consultation with various healthcare providers in outpatient settings (27, 28). Transitional care is an important part of interventions to prevent readmission of patients to healthcare centers and the provision of home-based and integrated healthcare services (29, 30). In transitional care, the actual environment and resources available in the patient home must be considered to achieve expected outcomes (31, 32). The results of previous systematic reviews showed that transitional care interventions improved self-management skills, reduced depression and readmission, and enhanced satisfaction (33, 34).

In developed countries, follow-up programs are carried out with various tools and technologies such as the telephone, which are implemented and continued for months after discharge and even lifelong care (35). Mobile technology is increasingly used in the field of health care (36). In recent decades around the world and with the development of data networks, mobile phones have become one of the most important technologies in providing health care. This technology is used for various purposes such as remote health control and self-management of health by patients with chronic conditions. Patients can use it for self-control and information exchange in various forms and in companionship with healthcare providers (37).

In Iran, the use of smart phones and the internet has increased significantly in recent years, so that almost all Iranian families benefit from these facilities (38). However, no action has been taken to benefit from the use of smart phones and popular social media platforms such as the WhatsApp on the mobile phone for the provision of transitional care from hospital to own home in cardiovascular patients. Therefore, it is necessary to take measures so that these patients can receive education, counseling, and follow-up at own home without the need for unnecessary referrals after discharge from the hospital.

Transitional care in previous studies have been carried out mostly in the form of follow-up after hospital discharge using telephone calls and sending short messages by carious healthcare providers. They have been mostly regardless of the capacities of patients and their family caregivers to perform care duties (39–45). In our study, nurses play a key role that is beyond the follow-up or discharge program. The transition care program in our study will begin before that the patient is discharged from the hospital and is transferred to own home, and will be developed based on the PCC approach with the coordination of patients and their families according to their needs and capacities. Therefore, this study is going to investigate the effect of a transitional care program from hospital to own home using the digital messaging application on self-efficacy, QoL, cardiac symptoms, and medication adherence among patients undergoing CABG surgery and caregiving burden.

## Methods

2.

### Design

2.1.

A parallel randomized controlled trial (RCT) study will be conducted on patients undergoing the CABG surgery in a hospital in a metropolis located in southwestern Iran. This protocol study was reported using Standard Protocol Items: Recommendations for Interventional Trial (SPIRIT) (46).

### Participants and sampling

2.2.

After a review of literature (41, 42, 47), eligibility criteria for the recruitment of patients include age over 18 years, CABG surgery for the first time, no other concomitant surgery during the CABG surgery, no history of respiratory diseases, no drug and alcohol addiction, no history of seizure, no psychological and cognitive problems, living with a family caregiver (spouse, children, siblings, other relatives) in own home, being literate as ability to read and write in Farsi, having a smartphone and ability to use WhatsApp, and signing the informed consent form to participate in the study.

In addition, inclusion criteria for family caregivers will be those over 18 years of age, being close family members of the patient, living with the patient, being literate as ability to read and write in Farsi, having a smartphone and ability to use WhatsApp, signing the informed consent form to participate in the study, ability to establish effective communication, experience of patient care undergoing the CABG surgery for the first time, and no history of mental health problems. Moreover, reluctance to participate, re-hospitalization, and patient death during the intervention will be exclusion criteria.

The required sample size has been separately estimated according to the study’s variables in the literature review including the QoL of CABG patients (41); cardiac symptoms (43); cardiac self-efficacy (48); medication adherence (49). The largest sample size (35 patients in each group) belongs to medication adherence using the following formula and its parameters:$$\begin{array}{c} N=\frac{{\left(z_{1-\frac{\alpha }{2}}+z_{1-\beta }\right)}^{2}*{\left(s_{1}+s_{2}\right)}^{2}}{{\left(\mu_{1}-\mu_{2}\right)}^{2}}\\ z_{1-\frac{\alpha }{2}}=1.96\;\;\;z_{1-\beta }=1.29 \end{array}$$μ_1_: The mean of the dependent variable in the intervention group.

S_1_: The standard deviation of the dependent variable in the intervention group.

μ_2_: The mean of the dependent variable in the control group.

S_2_: The standard deviation of the dependent variable in the control group.

α: Type I error.

β: Type II error.

Considering 10% attrition, the sample size will be 40 dyads of patients and caregivers in each group.

Sampling in the present study will be conducted sequentially and the dyads of the patient and family caregiver will be recruited. For the random allocation of the samples to control and intervention groups, a randomized block design of two treatments with quadruple blocks will be used. Second author (AM) will generate the random sequence using https://www.sealedenvelope.com. Sealed envelopes will also be used for concealment. An envelope will then be opened by the third author (RI) for each participant to assign them to the control or intervention group based on the card inside the envelope. The process of the study according to the Consolidated Standards of Reporting Trials (CONSORT) flow diagram has been presented in Figure 1.

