### Data analysis

2.6.

The two-sided primary statistical hypothesis will be tested as follows: transitional care program from hospital to own home using a digital messaging application has an effect on the health outcomes of patients undergoing CABG surgery and their family caregivers.

Data analysis will be conducted using descriptive and inferential statistics through SPSS statistical software version 25. Demographic and outcome data will be summarized as frequencies (percentages) or means (standard deviation) according to the level of measurement. To test the study hypotheses, the dependent variables will be cardiac self-efficacy, QoL, cardiac symptoms, medication adherence, and caregiver burden across three time points as at the baseline, immediately after the intervention, and two months after the intervention. Inferential statistical tests including repeated ANOVA test will be used. *P*-value will be set at *p* < 0.05. Furthermore, we will consider the intention to treat analysis for non-compliance or incomplete adherence (missing outcomes). Sensitivity analyses will be performed to assess the potential impact of non-response bias on our findings.

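### Re-hospitalisation, death and reluctance after randomisation are exclusion criteria, which conflicts with the intention-to-treat statement and selects the compared groups on an event that transitional care is said to reduce

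*Protocol article*

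**What the plan says.** Three parts of the Protocol article bear on this.

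- **Participants and sampling.** After the eligibility criteria for patients and caregivers, the section adds that "reluctance to participate, re-hospitalization, and patient death during the intervention will be exclusion criteria". It then sets the sample: "Considering 10% attrition, the sample size will be 40 dyads of patients and caregivers in each group", built up from 35 per group.
- **Data analysis.** The section says "we will consider the intention to treat analysis for non-compliance or incomplete adherence (missing outcomes"), and then "Sensitivity analyses will be performed to assess the potential impact of non-response bias on our findings". It does not say whether dyads excluded under the earlier rule are followed up or analysed. Outcomes are compared "at the baseline, immediately after the intervention, and two months after the intervention".
- **Introduction.** Follow-up after discharge under a transitional care programme "can reduce the readmission rate and the incidence of adverse events", and "Transitional care is an important part of interventions to prevent readmission of patients to healthcare centers".

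The Abstract gives the length of the intervention: "The intervention group will receive a transitional care program for 8 weeks using the WhatsApp".

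**The concern.** Re-hospitalisation and death during an eight-week programme can happen only after the envelope has been opened. Listing them as exclusion criteria therefore removes randomised dyads, whereas an intention-to-treat analysis keeps every dyad in its allocated arm. The clash is most literal for reluctance: a patient who loses interest during the programme is the kind of non-complier that the Data analysis section proposes to handle by intention to treat.

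Re-hospitalisation carries the main statistical risk. If the programme changes who is readmitted, removing readmitted patients takes different kinds of patient from each arm, and those who remain are no longer the randomised groups. The programme could plausibly change readmission in either direction: it may prevent some admissions, and asking patients about symptoms twice a week may prompt others. The loss is also avoidable, because the follow-up questionnaires are completed through WhatsApp and do not require the patient to be at home.

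**Working it through.** **1. Are these screening criteria or later exclusions?** Eligibility and consent are listed separately in the same section. The exclusion sentence places the events during the intervention, which follows allocation. Reluctance alone could mean refusal at the outset; re-hospitalisation and death during the intervention cannot. The window is also not defined for the control arm, which receives routine care and no eight-week programme.

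**2. Does the Data analysis section resolve it?** No. It names non-compliance, incomplete adherence and missing outcomes, and sensitivity analyses for non-response. It does not mention excluded dyads.

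**3. The plan's own sample size.** Inputs from Participants and sampling: 35 per group, 10% attrition.
- 35 / (1 − 0.10) = 38.9, rounded up to 39. The stated 40 is consistent with this.
- 40 × 0.90 = 36 remain, which covers 35.

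**4. If exclusions come on top of the 10%.** The article gives no re-hospitalisation rate, so r is assumed. Remaining per arm = 40 × 0.90 × (1 − r):

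| r | Remaining per arm |
|---|---|
| 0 | 36.0 |
| 5% | 34.2 |
| 10% | 32.4 |
| 15% | 30.6 |
| 20% | 28.8 |

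The break-even is 1 − 35/36 = 2.8%. For a two-sample t test at two-sided 5% and 90% power, the detectable difference rises from 0.775 SD at 36 per arm to 0.866 SD at 29. If the exclusions are already within the 10%, none of this applies.

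**5. Size of the selection bias.** Assume no true effect, and a latent tendency to avoid readmission that has correlation ρ with the outcome. Excluding the readmitted fraction p shifts an arm's mean by ρ × φ(z_p)/(1 − p), where z_p is the p-quantile of the standard normal distribution and φ its density.
- φ(z_p)/(1 − p) = 0.162 at p = 8%, 0.195 at 10%, 0.274 at 15%, 0.350 at 20%.
- Bias (intervention minus control) = ρ × [value for intervention − value for control].

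| Control vs intervention readmission (assumed) | ρ = 0.3 | ρ = 0.5 | ρ = 0.7 |
|---|---|---|---|
| equal rates | 0 | 0 | 0 |
| 15% vs 10% | −0.024 | −0.040 | −0.056 |
| 15% vs 8% | −0.034 | −0.056 | −0.079 |
| 20% vs 10% | −0.046 | −0.078 | −0.108 |

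A negative value runs against the programme, because the arm with fewer readmissions keeps more of its sicker patients. The sign reverses if the intervention arm is readmitted more. For scale, the standard error of a difference in means at 36 per arm is √(2/36) = 0.236 SD.

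**The case against.** The strongest defence is one of reading. The sentence stands in a section on recruitment and does not mention the analysis set. It could mean only that participation stops, leaving these dyads as missing-outcome cases for the intention-to-treat and sensitivity analyses. No text says that data already collected will be discarded. This shows that the wording is ambiguous, but it does not remove the conflict: the text says exclusion, and nowhere says that these dyads are followed or kept.

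The three events also differ. Some reluctance will be withdrawal, which the Ethical considerations section permits at any phase. A patient who has died cannot complete a questionnaire, so simply retaining the dyad does not settle how it is analysed. Both points stand and shape the fix.

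A reader might infer three stronger claims that the article does not support.
- **That the trial will be underpowered.** 40 less 10% leaves 36. A shortfall requires exclusions beyond the 10%, and attrition can naturally be read to include them.
- **That the result will be materially biased, or biased in favour of the programme.** Every rate and correlation above is assumed. A bias of 0.08 SD is about one third of the standard error (0.08/0.236 = 0.34), and where the programme lowers readmission it works against the programme.
- **That the exclusion discards one of the trial's own endpoints.** Readmission is not a listed outcome. That the programme may affect it rests on the Introduction's general account of transitional care.

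**Conclusion.** The conflict between the exclusion rule and the intention-to-treat statement is real and unreconciled. It matters most for re-hospitalisation, which occurs after randomisation and which the Introduction says transitional care can reduce. Its numerical consequence is probably modest: about 0.03 to 0.08 SD for 15% vs 8% readmission with correlation 0.3 to 0.5 and for 20% vs 10% with correlation 0.5. The wider assumed grid gives 0.02 to 0.11 SD, and equal rates give zero. The direction in the actual trial cannot be known from the article. Any fall below 35 per arm depends on exclusions lying outside the 10%. The case for acting does not rest on a large bias: follow-up data that are never requested from excluded dyads cannot be recovered at analysis.

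**What to change.** - **Analysis set.** Remove re-hospitalisation, death and reluctance during the intervention as reasons to exclude a dyad from the analysis. Replace the tentative intention-to-treat wording with a commitment that all randomised dyads are analysed as allocated.
- **Follow-up.** Keep sending both planned follow-up questionnaires, in both arms, to re-hospitalised dyads and to those who stop the programme, unless consent for data is withdrawn. This concerns data collection only and leaves open whether the programme itself continues for them.
- **Death.** Keep data collected before death and state how later outcomes are handled, for example by likelihood-based use of the observed data with a sensitivity analysis.
- **Reporting.** Give counts of re-hospitalisation, death and withdrawal by arm in the participant flow, without adding them as efficacy endpoints.
- **Sample size text.** State which losses the 10% attrition covers.

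The cost is protocol wording and some already planned questionnaires sent to a few more dyads. No extra recruitment and no change to clinical management is needed.

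### The printed sample-size formula squares the sum of the two SDs where it needs the sum of their squares; the error is conservative, and the document cannot show whether it entered the 35 per group

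*Protocol article*

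**What the plan says.** The Participants and sampling section reports that a size was estimated separately for quality of life, cardiac symptoms, cardiac self-efficacy and medication adherence, each from a literature source. It then states: "The largest sample size (35 patients in each group) belongs to medication adherence using the following formula and its parameters". The formula that follows is

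N = (z₁₋α/₂ + z₁₋β)² × (s1 + s2)² / (μ1 − μ2)², with z values of 1.96 and 1.29.

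The symbols are defined in words only. For example, μ1 is "The mean of the dependent variable in the intervention group" and s1 is "The standard deviation of the dependent variable in the intervention group". No value is given for any mean or SD, and no effect size or power percentage is stated. The section concludes: "Considering 10% attrition, the sample size will be 40 dyads of patients and caregivers in each group". Allocation is two-arm: "a randomized block design of two treatments with quadruple blocks will be used". The Data analysis section agrees with z = 1.96: "The two-sided primary statistical hypothesis will be tested as follows", and the significance level "will be set at *p* < 0.05".

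**The concern.** The difference between two independent group means, with n per group, has variance (s1² + s2²)/n. The numerator of a per-group formula must therefore contain s1² + s2². Squaring the sum of the SDs adds 2·s1·s2, which has no place there.

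This formula is the article's only sample-size justification. Because no inputs or target effect are printed, it is also the reader's only route back to the difference the trial was planned to detect. At equal SDs that route leads to about 1.10 SD with the formula as printed and about 0.78 SD with the standard one. The inflation also depends on the SD ratio, so it can differ between the four outcomes. If the printed form was applied, the ranking that puts medication adherence first needs rechecking.

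**Working it through.** **Inputs from the document:** z = 1.96 and 1.29; 35 per group; 10% attrition; 40 dyads per group. **Not in the document:** μ1, μ2, s1 and s2. SD ratios below are assumptions, shown as a range.

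**1. Reproducing the plan's figures.** The 35 cannot be computed forward, because the means and SDs are missing. The attrition step can be checked: 35/(1 − 0.10) = 38.9, so 39, against 40 stated. That is adequate, and 40 × 0.90 = 36 evaluable per group.

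**2. Size of the formula error.** Inflation factor f = (s1 + s2)² / (s1² + s2²) = 1 + 2·s1·s2/(s1² + s2²). For positive SDs, f is above 1 and at most 2, and equals 2 only when s1 = s2.

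**3. Difference implied by N = 35, equal SDs.** (1.96 + 1.29)² = 3.25² = 10.5625.
- Printed form: 35 = 10.5625 × 4/d², so d = √(42.25/35) = 1.099 SD.
- Standard form: 35 = 10.5625 × 2/d², so d = √(21.125/35) = 0.777 SD.

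**4. If 35 came from the printed form.** The same inputs in the standard formula need 35/f. Power with 35 per group (normal approximation) is Φ(3.25·√f − 1.96).

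| SD ratio | f | 35/f | N per group | Power with 35 |
|---|---|---|---|---|
| 1 | 2.00 | 17.5 | 18 | 99.6% |
| 1.5 | 1.92 | 18.2 | 19 | 99.5% |
| 2 | 1.80 | 19.4 | 20 | 99.2% |
| 3 | 1.60 | 21.9 | 22 | 98.4% |
| 5 | 1.38 | 25.3 | 26 | 96.9% |

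The noncentral t gives 99.5% in the first row. The power implied by z = 1.29 is 90.1%.

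**5. If 35 came from the standard form and the formula was misprinted.** The figure stands. Power at 0.777 SD is 90.1% by the normal approximation and 89.3% by the noncentral t.

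**6. Does the ranking of outcomes matter for adequacy?** The largest of the four sizes was 35. If all four came from the printed form, each corrected size is its printed size divided by a factor above 1, hence below 35. If all came from the standard form, none exceeds 35. So 35 covers all four, whichever ranks first.

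**7. What the planned numbers can detect.** With 36 evaluable per group, equal SDs and two-sided 5%, 90% power is reached at 0.775 SD by the noncentral t, or (1.96 + 1.2816) × √(2/36) = 0.764 SD by the normal approximation: about 0.77 SD.

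**The case against.** The strongest reply is that a misplaced exponent in a typeset formula proves nothing about the calculation behind it. That stands. A reader might infer that 35 is up to twice what its inputs require, but the inputs are not printed and the 35 cannot be traced to either form. The statement that 35 was obtained with this formula favours the printed form without settling it.

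A reader might also infer that the planned effect and power are misstated. The article states neither an effect nor a power percentage; power enters only as z = 1.29. The 1.10 and 0.78 SD figures are back-calculations under equal SDs, not claims made by the plan.

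A third tempting reading is that a null result could not be interpreted. What a null result excludes is read from the confidence interval for the observed difference, not from the planning formula.

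The value 1.29 in place of 1.2816 is not worth raising. It changes N by about 0.5% ((3.25/3.2416)² = 1.005), and 34.8 rounds back to 35.

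One defence of the formula fails. At equal SDs, (s1 + s2)² = 4s² would give the total for both groups, but the text labels the result as per group. On that reading the label is wrong instead of the formula, and 35 per group is again more than enough.

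**Conclusion.** The formula is incorrect as printed for a per-group size, and it overstates N by a factor above 1 and at most 2. Whether this reached the 35 cannot be determined from the article. If it did, the inputs needed 18 per group at equal SDs, rising to 26 at an SD ratio of 5, and power with 35 is about 97% to 99.6% over that range. If it did not, 35 is right for about 0.78 SD.

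The error can only enlarge the trial, so it does not leave it underpowered for the four sized outcomes. This rests on a single two-group comparison of means, the same form having been used for all four outcomes, and the literature values being taken as given. It says nothing about caregiver burden, which is not among the outcomes listed as sized. Severity is minor: the justification needs correcting, while recruitment and the planned analysis do not change.

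**What to change.** - Replace (s1 + s2)² with s1² + s2² in the formula.
- Rerun it for the four outcomes with the literature means and SDs already used, and print those values.
- State which form produced 35 and which outcome gives the largest size after correction.
- Keep 40 dyads per group. Add that about 36 evaluable per group give 90% power at two-sided 5% for a difference of about 0.77 SD, assuming equal SDs. Present this as the difference the chosen size can detect, not as the original target, since nothing in the article shows that 0.77 SD was what the trial was planned for.

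The cost is one formula and one paragraph, with no change in recruitment.
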